## Abstract

**Background:**

Physical inactivity is a leading risk factor for chronic disease. Brief physical activity counselling delivered within healthcare systems has been shown to increase physical activity levels; however, implementation efforts have mostly targeted primary healthcare and uptake has been sub-optimal. The Brief Physical Activity Counselling by Physiotherapists (BEHAVIOUR) trial aims to address this evidence-practice gap by evaluating (i) the effectiveness of a multi-faceted implementation strategy, relative to usual practice for improving the proportion of patients receiving brief physical activity counselling as part of their routine hospital-based physiotherapy care and (ii) effectiveness of brief physical activity counselling embedded in routine physiotherapy care, relative to routine physiotherapy care, at improving physical activity levels among patients receiving physiotherapy care.

**Methods:**

Effectiveness-implementation hybrid type II cluster randomised controlled trial with embedded economic evaluation, qualitative study and culturally adapted patient-level outcome measures. The trial will be conducted across five hospitals in a local health district in Sydney, Australia, with a lower socioeconomic and culturally diverse population. The evidence-based intervention is brief physical activity counselling informed by the 5As counselling model and behavioural theory, embedded into routine physiotherapy care. The multi-faceted strategy to support the implementation of the counselling intervention was developed with key stakeholders guided by the Consolidated Framework for Implementation Research and the Capabilities, Opportunities, Motivation-Behaviour (COM-B) theoretical model, and consists of clinician education and training, creating a learning collaborative, tailored strategies to address community referral barriers, team facilitation, and audit and feedback. Thirty teams of physiotherapists will be randomised to receive the multi-faceted implementation strategy immediately or after a 9-month delay. Each physiotherapy team will recruit an average of 10 patients (*n*=300) to collect effectiveness outcomes at baseline and 6 months. The primary effectiveness outcome is self-reported planned physical activity using the Incidental and Planned Exercise Questionnaire, and the primary implementation outcome is reach (proportion of eligible new physiotherapy patients who receive brief physical activity counselling). Secondary effectiveness and implementation outcomes will also be collected.

**Discussion:**

This project focuses on physiotherapists as health professionals with the requisite skills and patterns of practice to tackle the increasing burden of chronic disease in a high-risk population.

**Trial registration:**

ANZCTR, ACTRN12621000194864. Registered on 23 February 2021.

**Supplementary Information:**

The online version contains supplementary material available at 10.1186/s43058-022-00291-5.

Contributions to the literature
Physical inactivity is a leading risk factor for chronic disease and increases the economic burden on healthcare systems. Brief physical activity counselling embedded in healthcare can reduce physical inactivity, but implementation has been sub-optimal. This study addresses this important evidence-practice gap.This study will test both the implementation and effectiveness of brief physical activity counselling delivered by hospital-based physiotherapists to patients living in a lower socioeconomic and culturally diverse areas.This study will contribute to the recognised gap in the literature on diverse participant recruitment into trials by testing targeted approaches to recruit and retain patients from culturally and linguistically diverse populations.

## Background

Physical activity counselling refers to a component of patient consultation aimed at changing physical activity behaviour as a means of primary or secondary prevention of lifestyle-related chronic health conditions [1]. Physical activity counselling interventions that are underpinned by theoretical models of behaviour change and incorporate behaviour change techniques including identifying barriers, self-monitoring, goal setting and feedback have been shown to increase physical activity in the general population [2–4] as well as people with physical disabilities [5]. Brief physical activity counselling interventions such as the 5As approach (Assess, Advise, Agree, Assist and Arrange) [1] have shown to enhance physical activity with small to medium effects when delivered in healthcare settings by medical practitioners, practice nurses, physiotherapists and other healthcare professionals [6–8].

International [9, 10] and national [11] health organisations recommend that health professionals promote physical activity within their routine practice, and health professionals themselves strongly believe that they should be doing this [12, 13]. However, healthcare systems have failed to implement and scale-up physical activity promotion. Surveys of health professionals [12–15], audits of medical records [16] and surveys of patients [16–19] from around the world confirm that physical activity promotion, including counselling, is not routinely delivered in healthcare. Health professionals report that common barriers to delivery of this intervention include insufficient reimbursement, resources, time, knowledge, skills, training, protocols and organisational routines that do not support implementation [12, 13, 20, 21].

Physiotherapists are ideally placed to deliver physical activity counselling within their routine healthcare interactions. Physiotherapists can effectively deliver physical activity counselling [22], and patients see them as trustworthy physical activity messengers [23]. Physiotherapists have expertise in exercise prescription for a range of different health conditions and typically see patients on multiple occasions over an extended period which is ideal for supporting behaviour change [24]. Physiotherapists surveyed around the world agree that the promotion of physical activity should be part of their clinical role [25–28]. However, current efforts to put this into practice have been sub-optimal with only 36 to 54% of physiotherapists surveyed in different countries reporting they promote physical activity beyond therapeutic exercise to 10 or more patients per month [25, 26, 28]. Physiotherapists report similar barriers to implementation as other healthcare professionals [25–28].

The Brief Physical Activity Counselling by Physiotherapists (BEHAVIOUR) cluster randomised controlled trial will aim to address this evidence-practice gap by delivering a multi-faceted implementation strategy to teams of hospital-based physiotherapists to support them to implement brief physical activity counselling into routine care, which will, in turn, increase physical activity levels of patients receiving physiotherapy. A cluster design has been chosen to avoid the risk of contamination among individual physiotherapists working together within clinical teams. Although there is strong evidence for brief physical activity counselling in healthcare, few studies have been conducted with physiotherapists working in a public hospital setting, and few studies have been conducted in lower socioeconomic areas with patients from culturally and linguistically diverse backgrounds. Consequently, we cannot be certain that the implementation of brief physical activity counselling in this setting will increase the physical activity levels of the population of interest. Therefore, we will conduct an effectiveness-implementation hybrid type II study [29] with equal interest in implementation and effectiveness outcomes. This design is particularly suited to situations such as ours where there is good buy-in in the clinical setting, but intervention effectiveness is not yet known for this particular setting and population [30].

The co-primary effectiveness and implementation research questions are as follows:Do patients receiving physiotherapy care participate in greater amounts of planned physical activity at 6 months if their physiotherapist received the multi-faceted implementation strategy to support the implementation of brief physical activity counselling in routine care, compared to patients whose physiotherapist did not receive the multi-faceted implementation strategy (primary effectiveness outcome)?Do a greater proportion of patients receive brief physical activity counselling within routine physiotherapy care by physiotherapists who have received the multi-faceted implementation strategy compared to those who have not (reach, primary implementation outcome)?

Secondary research questions are as follows:Do patients receiving physiotherapy care participate in greater amounts of overall physical activity (self-reported, device-based [sub-sample]), report greater function and quality of life, fewer barriers to physical activity and better impressions of physiotherapy care at 6 months if their physiotherapist received the multi-faceted implementation strategy to support the implementation of brief physical activity counselling in routine care, compared to patients whose physiotherapist did not receive the multi-faceted implementation strategy?What is the adoption, reach, dose delivered, fidelity and sustainability of the delivery of brief physical activity counselling in routine physiotherapy care, and the delivery of the multi-faceted implementation strategy?What are physiotherapists’ experiences and reported barriers and facilitators to engage with the multi-faceted implementation strategy and delivering physical activity counselling within routine physiotherapy care?What is the cost-effectiveness of the multi-faceted implementation strategy and delivery of physical activity counselling in routine physiotherapy care?How successful are the targeted trial participation approaches for optimising participation of patients from Culturally and Linguistically Diverse (CALD) backgrounds in the trial, in terms of reach and retention?

We hypothesise that physiotherapists who receive the multi-faceted implementation strategy will be better able and more motivated to incorporate brief physical activity counselling into routine care (measured by reach, dose delivered and fidelity of the physical activity counselling) than physiotherapists who have not received the multi-faceted implementation strategy. In turn, we hypothesise that patients who receive their physiotherapy care from a physiotherapist who has participated in the multi-faceted implementation strategy will be more likely to achieve greater amounts of planned physical activity at 6-month follow-up than patients who receive physiotherapy care from a physiotherapist who has not yet participated in the multi-faceted implementation strategy. We also hypothesise that the multi-faceted implementation strategy will be a cost-effective way to achieve practice change and greater physical activity among patients.

## Methods

### Design

A cluster randomised controlled superiority trial with two parallel groups and 30 clusters will be undertaken. Qualitative and economic evaluation sub-studies, and cross-cultural adaptations of patient-level outcome measures will be embedded in the trial. The study will use an effectiveness-implementation hybrid type II design [29]. The trial design is presented in Fig. 1 and is guided by the Consolidated Standards of Reporting Trials (CONSORT): extension to cluster randomised controlled trials [31] and reported according to the Standard Protocol Items: Recommendations for Interventional Trials (SPIRIT) [32], the Standards for Reporting Implementation Studies (StaRI) Statement [33] and the TIDieR framework for evidence-based intervention description [34]. This study was approved by the South Western Sydney Local Health District Human Research Ethics Committee (2019/ETH13622; 2019/STE17765) and registered prospectively on the Australian and New Zealand Clinical Trials Registry (ACTRN12621000194864).

**Fig. 1 Fig1:**
[figure not shown]
Flow diagram of study design

### Consumer and health professional input

This study was co-designed with our clinical investigators (MJ, BB, BS) and refined with local health professional input including physiotherapy managers and senior and junior physiotherapists via informal consultations and site visits, and formally via survey [24] as part of pre-implementation work led by LH. Consultation with staff from the District Multicultural Health Service informed our targeted approaches to include diverse participants and consumer representatives from the District and our research Institute Consumer panels provided input on patient-facing resources.

### Study sites and participant groups

This trial will be conducted across the South Western Sydney Local Health District (SWSLHD), a large health district within the state of New South Wales, Australia. This district includes lower socioeconomic areas, services almost one million people in both suburban and rural communities, 51% of households speak a language other than English at home and physical activity levels are 9% lower than the state average [35, 36]. The health district includes five public hospitals employing approximately 166 physiotherapists, and this study will recruit through physiotherapy departments at all five hospitals.

#### Therapist inclusion criteria

A hospital clinical team that provides a service for inpatients or outpatients within SWSLHD and has one or more physiotherapists within the team will form each of the 30 clusters. The size of clinical teams is likely to be different across different areas of physiotherapy and hospitals. Examples of clinical teams likely to be recruited include musculoskeletal outpatients, inpatient rehabilitation and pulmonary rehabilitation. For the clinical team to be included in the trial there needs to be at least one physiotherapist within the team interested in participating and who meets the following eligibility criteria: they anticipate they will remain employed within SWSLHD for the next 12 months, are either permanent or on ≥ 6-month rotation in the identified clinical team, would treat ≥ 10 new eligible adult patients within their clinical team over a 3-month period and are not working in a split role across two clinical teams that have both been identified as potential clusters for the trial to avoid potential contamination.

#### Patient inclusion criteria

Patients will be recruited by the participating physiotherapists in each of the 30 clusters. Patient participants are likely to be affected by common and/or burdensome conditions such as, but not limited to, osteoarthritis, lower limb amputations, chronic pain, stroke, brain injury, cardiac and pulmonary disease. Patients will be eligible if they are at least 18 years old, are new patients of one of the participating physiotherapists during the recruitment period, live in the community (as opposed to residential care), able to leave their home without physical assistance from another person but may use a walking aid or wheelchair (anticipated within 6 months of recruitment), are without major cognitive impairment (e.g., diagnosis of dementia), do not have any medical reasons for which interventions aimed at increasing physical activity would be contra-indicated and have sufficient language capabilities to respond to written questionnaires in English, Arabic or Vietnamese.

### Recruitment and allocation

#### Clinical teams

Thirty clinical teams will be recruited as clusters and randomised to either the immediate-implementation group (who will receive the multi-faceted implementation strategy immediately) or the waitlist control group (who will receive an updated version of the multi-faceted implementation strategy at the end of the trial). Eligible clinical teams will be identified by the Chief Investigator (LH) in collaboration with the District Physiotherapy Director (MJ) and the Physiotherapy Head of Department at each hospital site. The Chief Investigator will present the study protocol at department meetings and the Head of Department will then liaise with their staff regarding interest and eligibility to participate. Physiotherapists within eligible teams who agree to participate will be consented prior to the team being randomised. The randomisation schedule will be generated and managed by the Clinical Trials Centre at The University of Sydney who are not involved in the recruitment of clusters to ensure concealed allocation. The randomisation schedule includes minimisation based on the average number of occasions of service delivered by each clinical team (high dose vs. low dose i.e. equal to or above vs. below the median number of occasions of service) [24]. When there is a team(s) to randomise, the Chief Investigator will email the Clinical Trials Centre who will complete the randomisation and email the team allocation within 24 h.

#### Patient-participants

Consecutive new patients of participating physiotherapists within the 30 clinical teams who meet the eligibility criteria will be invited to participate in the study by their treating physiotherapist. Each eligible patient will be provided with a written participant information sheet and encouraged to discuss their participation with family. At their next physiotherapy session, the physiotherapist will consent the patient and provide them with a paper-based survey to complete. The patients will be blinded to the implementation aspect of the study and told the focus is to evaluate how people recover and get back to activity after receiving physiotherapy care.

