### Multi-faceted implementation strategy

The multi-faceted implementation strategy will be delivered by the research team to clinical physiotherapists randomised to the immediate-implementation group within their clinical teams (where possible) to support them to incorporate brief physical activity counselling into their routine practice. The primary implementation strategies will include education, training, tailored strategies to address community referral barriers, creation of a learning collaborative across the district, team facilitation, and audit and feedback to build clinicians’ Capabilities, Opportunities and Motivations to deliver brief physical activity counselling within routine care (see Table 2).

**Table 2 Tab2:** Description of multi-faceted implementation strategy delivered to teams of physiotherapists mapped to Behaviour Change Wheel [37]

Implementation strategy [40]^**a**^	Mode of delivery/where/length/who delivered	Time-frame	Proposed mechanism of action			Intervention content	
			Barriers targeted	COM-B domains [41]	COM-B intervention functions	BCTs	Detailed explanation
Education	Series of short (2–8 min) education videos /online/~ 45 min in total/ LH, BB, research physiotherapists, consumers	Prior to attending workshop 1	Knowledge of PA guidelines, benefits of PA, consequences of inactivity, % meeting guidelines, what is PA counselling, what is the evidence for PA counselling and “what works” for supporting behaviour change, how many people to treat to have an effect, how many physiotherapists currently do it and if they don’t what stops them (include local data), what do patients think	Capability Psychological-knowledge; Motivation-reflective & automatic	Education; persuasion	Information about health consequences; Feedback on behaviour; Feedback on the outcome(s) of the behaviour; Information about others’ approval; Credible source; Salience of consequences; Feedback on behaviour; Social comparison; Identification of self as a role model	Short videos on the study, what is PA, what are the PA guidelines, benefits of PA from a patient perspective, what is PA counselling, behaviour change theories, raising the topic of PA as PT, raising the topic of PA with CALD patients

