### Data collection methods and outcome measures

As a hybrid type II study [29], patient-level effectiveness and implementation outcomes will be measured. All effectiveness outcomes (excluding device-measured physical activity and impressions of physiotherapy) as well as demographic information and co-morbidities will be assessed at baseline to enable a description of the patient-participant’s baseline characteristics and to obtain values to enter as covariates in the models comparing groups at follow-up. At the time of consent, the treating physiotherapist will provide the participant with a copy of the paper-based survey. This will be completed independently by participants or assisted by study staff over the telephone who are blinded to physiotherapy team allocation. At 6 months post-baseline, follow-up paper-based surveys will be mailed to participants and followed up by blinded research staff if surveys are not returned by mail.

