Adoption	The percentage and representativeness of providers (clinical teams) that will adopt physical activity counselling, will be measured by (1) The number of clinical teams across the district who participated compared to the number invited to participate; (2) Percentage of eligible physiotherapists within clinical teams who participated in the study (participated in implementation strategies and attempted to deliver physical activity counselling to their patients).	1. Audit of study records kept by research team 2. Study-specific training and resources log	Number of physiotherapy clinicians or managers across the district that contribute content, resources or teaching within the multi-facted implementation strategy.	Study-specific training and resources log
Dose delivered	The dose of physical activity counselling will be measured across immediate and waitlist groups by physiotherapist self-reported proportion of time spent on physical activity counselling within total usual care sessions for recruited patient participants in the trial.	Study screening log and hospital occasion of service statistics^b^	Average dose (hours) per clinical team of implementation strategies delivered (education and training, audit and feedback, facilitation sessions, learning collaborative, tailored strategies for community referral).	Study-specific training and resources log
Fidelity (adherence)	The fidelity of physical activity counselling (elements included) delivered to patient-participants will be measured across immediate and waitlist groups in two ways, self-report and audit.	1. Physiotherapist self-report study checklist^b^ 2. Audit of EMR of all patient-participants^b^	Fidelity of multi-facted implementation strategy delivered will be measured by the percentage of implementation strategies that are implemented as prescribed in the study protocol including modes of delivery; COM-B domains, categories and intervention functions; proposed content and behaviour change techniques.	Study-specific checklist
Sustainability (maintenance)	The sustainability of physical activity counselling (elements included) will be measured in intervention clinical teams in a random sample of patients (5 per team) after the patient recruitment period.	Audit of EMR	Percentage of clinical physiotherapists from immediate implementation group involved in delivering implementation strategies or providing resources to waitlist implementation group.	Study-specific training and resources log

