##### Patient-level effectiveness outcomes

The primary analysis will evaluate the effect of the multi-faceted implementation strategy to train, support and facilitate physiotherapists to deliver brief physical activity counselling as part of their routine care [targeted at the cluster level] on primary and secondary effectiveness outcomes. The main (intention-to-treat (ITT)) dataset analysed will be constituted of all patients recruited into the study irrespective of what amount of physical activity counselling they received from their treating physiotherapist. For the continuous outcomes, multiple linear regression will be used with a group (immediate-implementation vs. waitlist control) as the primary independent variable and baseline scores as a covariate. Binary logistic regression will be used to compare groups on dichotomous outcome measures with the group as the primary independent variable.

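### Physiotherapists who know their team's arm enrol their own patients, and the stated effectiveness model adjusts only for the baseline score, omitting the minimisation factor and collected prognostic variables

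*Protocol article*

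**What the plan says.** **Order of events.** Under Clinical teams: "Physiotherapists within eligible teams who agree to participate will be consented prior to the team being randomised". No corresponding order is given for patients. The strategy "will be delivered by the research team to clinical physiotherapists randomised to the immediate-implementation group"; waitlist teams receive it at the end of the trial.

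**Who enrols.** Under Patient inclusion criteria: "Patients will be recruited by the participating physiotherapists in each of the 30 clusters". Under Patient-participants, consecutive eligible new patients "will be invited to participate in the study by their treating physiotherapist", and then: "At their next physiotherapy session, the physiotherapist will consent the patient and provide them with a paper-based survey to complete".

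**Who is blinded.** Patients (to the implementation aspect), staff who help with surveys, the multicultural health workers, and the analysts for the primary analyses. No blinding is stated for the people who identify or enrol patients.

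**Model.** Under Patient-level effectiveness outcomes, continuous outcomes are analysed by linear regression "with a group (immediate-implementation vs. waitlist control) as the primary independent variable and baseline scores as a covariate", within a GEE framework with exchangeable correlation. The analysis set is everyone recruited. Teams are allocated by minimisation on high versus low occasions of service, and that factor is not named in the model. Data collection methods and outcome measures says that most effectiveness outcomes "as well as demographic information and co-morbidities will be assessed at baseline", both for description and to supply covariates, without saying which variables enter.

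**The concern.** Randomising teams balances teams in expectation. It does not balance the patients enrolled afterwards if the enrolling staff know the arm. Physiotherapists trained to discuss activity may apply judgement-based criteria differently from untrained colleagues, or introduce the study differently. Two such criteria are the expected ability to leave home within 6 months and the absence of a medical reason against activity interventions. Intention-to-treat does not help, because the analysis set is whoever was enrolled.

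If the enrolled groups differ in expected 6-month planned activity at the same baseline score, the stated model reports that difference as part of the effect of the strategy. A larger sample would not remove it. Baseline-score adjustment removes only the part that the baseline score carries. Because consent and the baseline survey come a session after the invitation, counselling could also begin before baseline is recorded.

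**Working it through.** **1. Is enrolment after allocation, by unblinded staff?** This is implied, not stated. Physiotherapists consent, the team is randomised, immediate teams are trained, and the outcome compares patients of trained and untrained physiotherapists. Patients are enrolled as new patients during a recruitment period by those same physiotherapists. One sentence points the other way: Exploratory subgroup analysis says that all subgroups use data collected before randomisation. That cannot hold for gender, age or language of patients enrolled after their team's allocation, so it needs reconciling.

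**2. Reproduce the plan's sample size.** Inputs from Sample size: difference 1.5 h/week, SD 4.4, alpha 0.025 (sidedness not stated; two-sided assumed), power 80%, 15 clusters of 10 per arm, baseline correlation 0.6 (the plan's baseline-covariance term), ICC 0.05.
- Individual randomisation: n = 2 × [4.4 × (2.241 + 0.842) / 1.5]² = 163.6 per arm.
- Design effect: 1 + (10 − 1) × 0.05 = 1.45.
- Baseline adjustment: 1 − 0.6² = 0.64.
- n = 163.6 × 1.45 × 0.64 = 151.8 per arm, or 304 in total against the stated 300. Power at 150 per arm is 79.5%.

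The plan's figure reproduces, so the sample size is not in question.

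**3. Standard error of the adjusted difference.** Residual SD = 4.4 × √0.64 = 3.52. SE = 3.52 × √(2 × 1.45 / 150) = 0.489 h/week.

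**4. Effect of a residual selection shift b.** With no true effect, the two-sided false-positive rate is P(|Z + b/0.489| > 2.241). The values of b are assumptions.

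| b (h/week) | share of 1.5 h target | false-positive rate |
|---|---|---|
| 0 | 0% | 2.5% |
| 0.15 | 10% | 3.2% |
| 0.30 | 20% | 5.4% |
| 0.50 | 33% | 11.2% |
| 0.75 | 50% | 23.9% |

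Using a t distribution with 28 df and counting only results in the direction of the shift, the rate goes from 1.25% to 4.9%, 10.3% and 21.9% at 0.30, 0.50 and 0.75.

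**5. What would produce such shifts?** Take a trait that is not in the model, with correlation ρ with the outcome given baseline and differing by δ SD between arms. Then b = ρ × δ × 3.52.
- ρ = 0.3, δ = 0.3: b = 0.32 h/week, rate 5.7%.
- ρ from 0.2 to 0.4, δ from 0.2 to 0.5: b from 0.14 to 0.70, rate from 3.1% to 21.1%.
- At ρ = 0.3, b = 0.50 needs δ = 0.50 / (0.3 × 3.52) = 0.47, and b = 0.75 needs δ = 0.71. The top of the range therefore needs a large imbalance.

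**The case against.** The plan does contain safeguards. A reader might infer that physiotherapists are free to choose whom to approach. They are not: consecutive eligible patients are to be invited under written criteria, and selecting among them would breach the protocol. Patients are blinded to the implementation aspect, which limits arm-dependent refusal, and the screening spreadsheets are shared with the research team. All of this lowers the risk. It does not exclude it, because the same unblinded person applies the criteria, introduces the study and takes consent.

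Covariate choice is often left to the analysis plan, and the data-collection section can be read as already allowing demographics and co-morbidities. That reading is fair. However, the analysis section does not stay silent: it names the model terms, and the two sections do not say the same thing.

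A reader might also infer that the bias favours the strategy. The documents do not support a direction, since trained staff could equally enrol inactive patients who seem to need counselling.

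Nor do the documents show a ready-made external check on the logs. The source in Table 3, "Study screening log and hospital occasion of service statistics", serves dose delivered in recruited participants. It is not described as a list of all new patients, and no provision for data on people who decline is described.

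Finally, the added covariates do not measure motivation, and co-morbidity is at best a partial proxy for fitness. This stands, and limits what adjustment can achieve.

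**Conclusion.** The point holds as a moderate design weakness with a cheap partial remedy. Differential enrolment is possible and not excluded, and the stated effectiveness model omits both the minimisation factor and prognostic variables already collected. The protocol's own figures give a standard error of about 0.49 h/week, so residual shifts of 0.15 to 0.75 h/week would take the two-sided false-positive rate from 2.5% to about 3% to 24%. That range rests on assumed shifts, two-sided testing, equal clusters of 10, no loss to follow-up and a normal approximation. It is not an estimate of what will happen. The documents do not show that selective enrolment will occur, how large it would be, or which arm it would favour.

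**What to change.** 1. In Patient-level effectiveness outcomes, adjust the primary effectiveness model for the minimisation stratum (high/low occasions of service) and a short prespecified set of collected baseline variables: age, gender, language spoken at home, co-morbidity and inpatient/outpatient setting, in addition to the baseline score. Keep the baseline-score-only model as a sensitivity analysis.
2. Make the covariate statement in Data collection methods and outcome measures agree with this list, and reconcile the pre-randomisation wording in Exploratory subgroup analysis with the order of patient enrolment.
3. State that adjustment corrects measured imbalance only, and that differences in motivation may remain.
4. From the existing screening logs, report eligible, invited and consented numbers by arm, and compare the baseline characteristics of enrolled patients by arm.

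Cost: wording and tabulation. No extra patients, visits or staff are needed, and the target of 300 is unchanged. The statistical price is a few degrees of freedom with 30 clusters. Two of the added terms (stratum and setting) are team-level, taking the between-team degrees of freedom from 28 to 26, so the list should stay short.
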